**Objectives: see grant application form.**

## **2.2 APPROACHES, HYPOTHESES AND CHOICE OF METHOD**

### **2.2.1 Study design**

We propose a factorial (2x2), multi-center, assessor-blind pragmatic RCT to evaluate the longitudinal effect of MT in NICU and/or after discharge on premature infants and their primary caregivers across a 12-month time period (Fig. 1). The factorial design will allow testing the independent effect of each combination: NICU-MT, post-discharge MT, both, or neither, as well as interactions between them. Participants will initially be recruited from the NICU of participating hospitals according to the following in- and exclusion criteria:

- (1) Infants: Born below 35 weeks GA, of both genders, any ethnicity, from single or multiple pregnancies, who have achieved sufficient medical stability (as determined by medical staff) to start MT.
- (2) Primary caregivers: One of the parents/caregivers must provide written, informed consent before any study procedures occur. Primary caregivers should agree to engage in at least 2 of the 3 MT sessions per week during NICU, and/or in 5 of the 7 MT post-discharge sessions. To ensure feasibility, primary caregivers should live within reasonable commuting distance from the treating NICU in order to be eligible for participation.

The 2x2 factorial design entails a two-phase protocol covering both the stay in the NICU and municipal care after discharge from hospital. During NICU stay, participants will be randomly allocated to receive either MT integrated in standard NICU care or standard NICU care alone. Before discharge to home, participants will again be randomly allocated to either MT integrated in municipal care or standard municipal care. Standard care may include other early intervention methods of care with the exception of other music-based approaches. Treatment fidelity (adherence and competence) will be evaluated by independent raters using video recordings.

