**Power calculation and sample size:** No previous RCT examined effects of MT on the PBQ; two small RCTs included in our systematic review [25] and a recent non-randomized study [29] examined mother-infant bonding, but provided insufficient data for meta-analysis. Studies using the PBQ with other interventions found effects ranging from around 0.25 ([44], posttest) through 0.5 ([45], mothers at 1/6 months), 1.4 ([46], 4 months), 2 ([45], fathers at 1/6 months), 9 ([44], 3 months), with SDs ranging from 4 to 12. Assuming a difference of 4 points on the PBQ ( $SD = 8$ ) as a minimal clinically important difference for this study, power of 80% will be achieved for each main effect (each tested on a two-sided 2.5% significance level, i.e. 5% with Bonferroni correction for two tests) with a sample size of 155. Taking into account some clustering by country (ICC 0.01; 5 countries), this is increased to 203. To allow for 20% attrition, we will aim to include 250 infants (50 in each country) and their parents. This sample size will also ensure power for testing proportion differences of about 15% (e.g. binary analysis of problematic bonding; re-hospitalization). Special considerations are needed for multiple pregnancies (twins, triplets, etc.), which account for about 2% in Hordaland [4], but are more common in NICUs due to their elevated risk of preterm birth. Including all siblings would serve to increase the sample size, but may lower the resulting power due to cluster effects.

Therefore, we will only formally enroll and analyze the first-born sibling of each multiple pregnancy, although all will receive the intervention.

**Data analyses:** All randomized participants will be included in the main analysis (intention-to-treat). Descriptive statistics will characterize basic properties of the sample and provide information for power calculation for the multi-center study. Effects will be examined by testing the randomized groups for differences in the primary endpoint (t-test or Mann-Whitney; change in PBQ scores to 6 months CA), as well as by fitting linear mixed models. In the first modeling step we will assess the effect of the first randomization (Fig. 1) using the following model:

$$PBQ_{it} = \beta_0 + \beta_1 time_t + \beta_2 gr_i + \beta_{12} time_t gr_i + U_i + \varepsilon_{it} ,$$

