where  $PBQ_{it}$  denotes the PBQ score for participant  $i$  at measurement  $t$ ,  $time_t$  the time from baseline at measurement  $t$  and  $gr_i$  the randomization group of participant  $i$ .  $\beta_0$ ,  $\beta_1$ ,  $\beta_2$  and  $\beta_{12}$  are the coefficients estimated in the model,  $U_i$  is an individual random term per participant and  $\varepsilon_{it}$  an independent, identically distributed error term. In the second step we refine the model to take into account both randomization steps, leading to the extended model:

$$PBQ_{it} = \beta_0 + \beta_1 time_t + \beta_2 grR1_i + \beta_{12} time_t grR1_i + \beta_3 grR2_i + \beta_{13} time_t grR2_i + U + \varepsilon_{it} ,$$

with the same notation as above and  $grR1_i$  and  $grR2_i$  denoting the groups from the first and second randomization, respectively. In these models  $\beta_1$  describes a group-independent time effect,  $\beta_2$  and  $\beta_3$  a time-independent group effect, and  $\beta_{12}$  and  $\beta_{13}$  the time-dependent change of the group effect. We will investigate both linear and simple contrasts (comparing each time point with the baseline) in time to assess the treatment effect. The same analyses will be done for the secondary outcomes; using an analogous generalized linear mixed model for binary outcomes. Per-protocol analyses will include those who received at least 6 MT sessions in the NICU and at least 5 MT sessions post-discharge, respectively; these are considered the minimum numbers for the intervention to be successful. Additionally, we will conduct exploratory statistical analyses for prespecified subgroups (sex; GA at birth [ $<28$  wks, 28 to  $<32$  wks, 32 to  $<35$  wks]; hearing status at discharge [normal vs. abnormal]; bonding at baseline [PBQ impaired bonding score  $\geq 11$  vs.  $<11$ ]) as well as qualitative/mixed-methods analyses of process data to maximize learning.

**Data management plan:** To promote transparency and applicability of trial results and to facilitate re-analysis by other researchers while also protecting anonymity, de-identified individual patient data will be made available through the Norwegian Centre for Research Data (NSD).

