| Delineation of "PBQ at baseline" sub-groups                     | "bonding at baseline (PBQ impaired bonding score $\geq 11$ vs $< 11$ )"                                     | "bonding at baseline (PBQ impaired bonding score $> 11$ vs $\leq 11$ )"

[Date of change 1 January 2020]                                                                                                                                                                                                                                                                                                                                                                                                                                                 | To correct a typographical error                                                                                                                                                                                                                                                  |
| Implementation of intervention: MT post-discharge from hospital | "[MT post-discharge sessions]...will occur at home, municipal child health centres or follow-up clinics..." | Addition: "If in-person visits are not possible due to restrictions accompanying the COVID-19 pandemic, MT sessions post-discharge will be offered via videocalls. Procedures for the videocalls will follow the steps provided in the original protocol, with the exception that the music therapist will generally listen and observe when the parent is singing, instead of singing or providing musical accompaniment. Sites should return to offering in-person sessions, once that option becomes available again."

[Date of change 1 April 2020] | Social isolation restrictions related to the COVID-19 pandemic impacted all participating sites and precluded use of in-person MT sessions. On April 1, 2020, the study received approval from the overseeing ethics committee to incorporate procedures for virtual MT sessions. |

35

36

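### Exploratory effect modification by baseline bonding and gestational age is planned only in categories, with no continuous modifier and no interaction test stated

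*Combined protocol and SAP*

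**What the plan says.** The data analyses paragraph of section 2.2.4 plans "exploratory statistical analyses for prespecified subgroups (sex; GA at birth", among others. GA is divided as "GA at birth [ $<28$ wks, 28 to $<32$ wks, 32 to $<35$ wks". The bonding subgroup is given as "bonding at baseline [PBQ impaired bonding score", with two groups cut at 11. The summary of amendments to the published study protocol moves a score of exactly 11 into the lower group and gives the reason as "To correct a typographical error". The modifier remains a two-way split.

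Neither linear mixed model in section 2.2.4 contains a modifier term. The first has time, group and their product. The second adds the second randomization in the same way. The text does not say how subgroups will be compared, whether by an interaction test, by separate estimates or otherwise. Power is claimed for the two main effects and for differences in proportions, but not for effect modification, which is also absent from the primary and secondary objectives.

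**The concern.** GA and the impaired bonding score are numerical measures. A cut-off treats a parent just above it as different in kind from one just below it, and as the same as one far above it. If the benefit of music therapy rises or falls gradually with initial bonding or with maturity at birth, categories use less of the data than a continuous term does. If few parents lie above 11 at baseline, one group is also small.

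The bonding modifier is on the same instrument as the primary outcome. Enrolment is deliberately broad in GA ("Born below 35 weeks GA, of both genders, any ethnicity"), and therapy is tailored to postmenstrual age. Both modifiers are therefore worth examining well, even as exploratory questions. What is at stake is a real gradient being reported as no evidence of effect modification. Without a stated interaction test, there is also the risk that subgroup results are compared informally, by which group reaches significance.

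**Working it through.** **The plan's own figure.** The documents give no figure for the subgroup analyses, so only the design inputs can be checked. Section 2.2.4 starts from "Assuming a difference of 4 points on the PBQ", with SD 8, two-sided 2.5% and 80% power.

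- Normal approximation per arm: 2 × (8 × (2.241 + 0.842)/4)² = 76.04, rounded up to 77, or 154 in total. The t-based solution is 154.6, so the stated 155 reproduces.
- Clustering: 1 + (31 − 1) × 0.01 = 1.30. 155 × 1.30 = 201.5 and 156 × 1.30 = 202.8, against a stated 203.
- Attrition: 203/0.8 = 254, against 250 (within 3%). 250 × 0.8 = 200 analysed.

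**Bonding split, normal score.** If the effect changes linearly with the score, a two-group comparison keeps a share of information equal to the squared correlation between the score and the group indicator: φ(z)²/(p(1 − p)). Here p is the share above the cut and z the matching normal quantile. The documents do not give p, so it is varied. The third column is the equivalent number out of 200 analysed. The last is the power of the split when the continuous interaction test has 80% at two-sided 5%: Φ(2.802 × √efficiency − 1.960).

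| p above cut | Efficiency | Equivalent of 200 | Loss | Power of split |
|---|---|---|---|---|
| 50% | 0.3989²/0.25 = 0.637 | 127 | 36% | 61% |
| 30% | 0.3477²/0.21 = 0.576 | 115 | 42% | 57% |
| 20% | 0.2800²/0.16 = 0.490 | 98 | 51% | 50% |
| 10% | 0.1755²/0.09 = 0.342 | 68 | 66% | 37% |

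At 5% above the cut the loss would be 78%.

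**Bonding split, right-skewed score.** The general form is between-group variance of the score divided by its total variance. For gamma scores:

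| Share above cut | Loss, shape 1 | Loss, shape 2 |
|---|---|---|
| 50% | 52% | 45% |
| 30% | 38% | 36% |
| 20% | 35% | 37% |
| 10% | 41% | 47% |
| 5% | 53% | 60% |

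The range is therefore about 35% to 60%, and the two-thirds figure belongs to the normal case only.

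**GA in three bands.** The same variance ratio applies, with cuts at 28 and 32 weeks. The GA distribution is assumed, because the documents do not give it.

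- Normal, truncated to 23 to 35 weeks: 17.5% to 17.6% (mean 31 or 30, SD 3); 20% to 22% (mean 30, 31 or 32 with SD 2.5, or mean 34 with SD 3); 28% when three quarters fall in the top band (mean 36, SD 3).
- Untruncated normal with given band shares: 21% for equal thirds, 24% for 15/35/50, 30% for 10/30/60.
- Extremes tried: 12% if GA is uniform over 23 to 35 weeks, 37% for a very uneven 7/23/70.

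Most cases lie between about 17% and 30%.

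**The case against.** The strongest counter-argument is that the result rests on a linear gradient. The squared correlation works in both directions: if the true effect is a step at 11, the linear term keeps only 34% to 64% of the information of the split (normal score, 10% to 50% above), and the planned analysis is the better one. Section 2.2.3 describes the PBQ as a screening instrument, so a clinical cut-off is a defensible and readable choice. This stands. It is the reason to keep the categories and to check for non-linearity, but not a reason to have categories alone.

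It is also fair that the plan calls these analyses exploratory, claims no power for them, and provides for sharing de-identified data, so a continuous analysis could be done later. This limits the importance of the point. It does not favour the less informative method when the alternative needs no new data.

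Three stronger readings are tempting, and the documents do not support them:

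- A reader might infer that the loss of a third to two thirds applies to GA as well. GA has three bands, and the loss is mostly well below that range.
- A reader might infer that effect modification is tested by splitting and is a central question of the trial. No test is stated, and no objective mentions it.
- A reader might take the change at a score of 11 as evidence that results hinge on the boundary. It is a logged typographical correction and shows nothing about results.

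**Conclusion.** The point holds as an inexpensive improvement to exploratory analyses. Two numerical modifiers are planned only as categories, and no interaction test is specified. Under a roughly linear gradient, the bonding split loses about 36% to 66% of the information for a normal score with 10% to 50% above the cut, or about 35% to 60% for the right-skewed scores tried. The GA bands lose mostly about 17% to 30%. All of these rest on assumed distributions and an assumed share above the cut. They do not show that a gradient exists or that the plan would miss one, and under a step effect the comparison reverses. The primary comparison of PBQ at 6 months corrected age and its sample size are unaffected.

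**What to change.** In the data analyses paragraph of section 2.2.4, state for each of the two randomizations, and for the PBQ endpoint at 6 months corrected age, that effect modification will be tested with:

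1. treatment × continuous baseline PBQ impaired bonding score (the measure already named, not the 0 to 125 sum score);
2. treatment × GA at birth in weeks;
3. a quadratic or spline check for non-linearity in each.

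Keep the prespecified cut-off and the three GA bands for displaying subgroup estimates with confidence intervals, and report the interaction estimate rather than separate significance tests by group.

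The cost is a few sentences and a few model terms, using data already collected. The downside is lower power than the split if the effect is truly a step at the cut-off. The non-linearity check and the retained categories cover this in part.

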### 2.3 APPLICABILITY OF THE RESULTS OF LONGSTEP

The pragmatic nature of this trial and its high clinical applicability are reflected in several dimensions, as described in the pragmatic-explanatory continuum indicator summary (PRECIS) [47]. Eligibility criteria are designed to be as inclusive as possible to promote applicability of the evidence with respect to a broad population. Broad inclusion criteria ensure enrolment of participants with heterogeneous characteristics similar to those seen by clinicians in daily practice, and exclusion criteria are narrow and exist to ensure infant safety. Another pragmatic dimension of this trial is flexible MT delivered by a qualified music therapist. Instead of including infants in a narrow PMA range, we broaden the range of inclusion and instead tailor MT to infant PMA, while incorporating family and cultural preferences. Additionally, we do not restrict if or how co-interventions will be delivered. Both parallel groups will receive standard care. Analysis of primary outcome will include all individuals regardless of compliance in order to test if the intervention works under usual conditions, with all the noise inherent therein. As a limitation it should be noted that clinical benefits as well as resulting societal benefits, related to disability prevention and economic outcomes, are likely to occur over a longer-term perspective. To address this, we will also include the possibility in the consent forms to collect later follow-up data, but these will be beyond the present project. In summary, this pragmatic trial will determine the effects of MT under usual conditions, and the design as a multicenter trial will further ensure wide generalizability.

## 3. THE PROJECT PLAN, PROJECT MANAGEMENT, ORGANIZATION AND COOPERATION

**3.1 PROJECT PERIOD, PROGRESS PLAN, MAIN ACTIVITIES, MILESTONES:** see grant application form.

**Recruitment strategy:** The sites listed above vary between 13 and 60 beds and between 250 and 500 admissions per year. Following a pilot cohort at one site, an 18-month period for recruitment will be sufficient to achieve the targeted sample size. Each site will aim to recruit about 50 infants and their parents; therefore, slow recruitment at some sites will be tolerable. Recruitment rates will be monitored carefully. Local and national partners responsible for primary care provision, such as Bergen Municipality in the Bergen area, will serve as contact points after discharge and will be actively involved wherever possible.

**Other partners:** King's College London, UK ([name], senior lecturer, King's Health Economics) will be responsible for service use and costs with a view towards evaluating cost-effectiveness.

CVs of the most central researchers in the team are enclosed, demonstrating the range of expertise relevant to the project. Letters of intent from partners have been collected but are not enclosed.

As a *user representative*, [name], mother of two preterm infants and connected to Prematurforeningen, will help to ensure the project's user relevance. An *international scientific advisory panel* of clinicians and researchers with relevant clinical expertise will include [name] (University Hospitals Zurich and Bern, Switzerland); [name] (Temple University, USA); [name] (University of Kansas, USA); [name] (University of Gdansk, Poland); [name] (Mount Sinai Beth Israel and Icahn School of Medicine at Mount Sinai, USA); and [name] (Kantonsspital Baden, Switzerland). An *independent Data and Safety Monitoring Committee* consisting of clinicians and methodologists with relevant expertise but no direct involvement in the trial will be established to ensure research integrity and safety of participants in the trial, and will recommend appropriate action if ethical issues arise.

**3.3 BUDGET:** see grant application form. Contributions to partner sites are primarily through per-patient costs, adjusted to the price level of each country; this provides a fair and balanced allocation of resources and helps to boost recruitment.

#### 4. KEY PERSPECTIVES AND COMPLIANCE WITH STRATEGIC DOCUMENTS

**4.1 COMPLIANCE WITH STRATEGIC DOCUMENTS:** Research relevant to music and health is a focus area of Uni Research Health, and high-quality RCTs that can inform health services are the mainstay of its research agenda. This project improves caregiver sensitivity to premature infant signals and needs, and supports development of healthy infant/parent relations during the postnatal period consistent with national guidelines [31].

**4.2 RELEVANCE AND BENEFIT TO SOCIETY:** The project's social impact includes filling gaps in knowledge regarding the long-term impact of MT with preterm infants/caregivers, including impact on the highly user-relevant outcomes of bonding, infant development, and parental psychological health. The high applicability of this trial will facilitate ongoing development of evidence-based care for preterm infants. The project makes a unique contribution to continuity of care, by bridging intervention from NICU hospitalization to municipal and home settings post-discharge. Findings will impact families and children in a high-risk group, as well as music therapists, psychologists, medical staff, and municipal health care workers. Dissemination of the findings will apply to local, national, and international levels.

**4.3 ENVIRONMENTAL IMPACT:** not applicable.

**4.4 ETHICAL PERSPECTIVES:** Ethical approval will be secured before start of recruitment from the Regional Committee for Medical Research Ethics in Western Norway (REK Vest), as well as data security clearance from NSD, and corresponding bodies in the other participating countries. The study will be registered in the ISRCTN database before the first patient's first visit. Informed consent will be obtained postnatally following routine practices in the NICU. Trial staff will inform parents/caregivers about consent for participation. The parent/caregiver will receive written and oral explanation of the proposed research project including aims, duration of involvement, expected benefits to participants and others, nature of the interventions, procedures involved in participation, and any potential risks. It will be emphasized that enrolment in the study is voluntary, that parent/caregivers can withdraw at any time from all or part of the study, and that any decision they take in this respect will have no bearing on the care the infant and family receive. Participants will be informed that the outcomes of the study will be published, but that no details will be divulged from which the participant could be identified. The primary caregivers will also be informed who to contact in an emergency and how to discontinue participation if desired. The consent form will be available in Norwegian and English, and other participating countries will create translations as needed. All significant harms as well as unintended effects for each group will be collected and described. Special forms to report trial-related adverse events will be developed, and all professionals involved in the trial will be informed about how to identify and report adverse events. Any serious adverse effects that occur will be reported, and if related to MT, will be reported to the DMC.

**4.5 GENDER ISSUES (RECRUITMENT OF WOMEN, GENDER BALANCE AND GENDER PERSPECTIVES):** Both boys and girls born prematurely will be included. Primary caregivers of both genders will be included in this trial, although we anticipate that predominantly mothers will be participating in MT sessions. The gender distribution of researchers in the core team and among collaborators is balanced. The role of PI will be handed to a female researcher after the first year (see above).

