#### **2.2.4 Trial procedures, statistical considerations, and data management**

**Randomization, allocation concealment and blinding:** After informed consent and baseline assessment, participants will be randomly assigned to NICU-MT or standard care using a computer-generated randomization list, with ratio 1:1, in blocks with sizes of 2 or 4 varying randomly, using email and an online system. The random allocation sequence will be generated and administered by people with no involvement in the clinical work to ensure allocation concealment. One day before discharge to home, participants will be randomized a second time to post-discharge MT or standard care in a 1:1 ratio, using the same procedures. This two-step randomization was chosen as the best way to create balance among those remaining in the study for the aftercare phase, and to avoid differential drop-out in the NICU phase due to expectations for the aftercare phase. In multiple pregnancies, only the first-born infant will be included and randomized, while remaining siblings will receive the same interventions for ethical and practical reasons. Blinding of interventions is not possible, but all outcomes that are not self-reports will be blinded, and success of blinding will be tested.

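### The only stated route to the monitoring committee is for serious adverse effects related to MT, so the plan does not provide it with a comparison of harms between arms

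*Combined protocol and SAP*

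**What the plan says.** The rule is in Section 4.4 (Ethical perspectives): "Any serious adverse effects that occur will be reported, and if related to MT, will be reported to the DMC". All serious effects are to be reported, to a recipient who is not named. Those related to MT also go to the committee.

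Two other sentences in Section 4.4 bear on this. One promises collection in every arm: "All significant harms as well as unintended effects for each group will be collected and described". It names no recipient and no timing. The other concerns the forms: "Special forms to report trial-related adverse events will be developed". They do not yet exist, and their stated scope is events related to the trial.

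Section 3, in the paragraph on other partners, describes an independent Data and Safety Monitoring Committee, which I take to be the DMC of Section 4.4. It "will be established to ensure research integrity and safety of participants in the trial, and will recommend appropriate action if ethical issues arise". The section does not list the data the committee receives, and it mentions no by-arm table, meeting schedule or stopping guideline.

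On design, Section 2.2.1 sets out a 2x2 factorial with two successive randomizations, and Section 2.2.4 states that "Blinding of interventions is not possible". The amendment tables at the end of the document do not touch safety reporting.

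**The concern.** The plan's own background (Section 2.1) describes preterm infants as having raised mortality, morbidity and postnatal complications. Serious events will therefore occur in every arm for reasons unrelated to MT. In such infants a single event can seldom be attributed with confidence to a therapy session, or cleared of it. A harmful effect would show mainly as a higher rate in one randomized arm than in the other.

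A rule that forwards an event only after it has been linked to MT works against seeing that. It filters the MT events through a judgement that can be made with the allocation known, and it supplies no comparator. If MT raised the rate of serious events without any one case looking attributable, the body charged with participant safety would not learn of it by the stated route while infants were still being enrolled and treated. A description by group in the final report would come too late for them.

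**Working it through.** The plan states no figure on this point, so there is nothing to reproduce. The check is mainly structural, followed by an illustration of what by-arm review could show.

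**Who can send an event to the committee by the stated route**

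Inputs: planned N = 250, 1:1 allocation at each of two randomizations, the second one day before discharge (Sections 2.2.3 and 2.2.4, under randomization and power). Standard care excludes other music-based approaches (Section 2.2.1). The counts ignore losses before the second randomization.

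- Each level of a factor: 250 / 2 = 125.
- Each cell of the 2x2: 250 / 4 = 62.5, about 62.

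| Period | Group | About | Can an event qualify as related to MT? |
|---|---|---|---|
| NICU stay | NICU-MT | 125 | Yes, if attributed |
| NICU stay | Standard care | 125 | No, no study MT yet received |
| After discharge | Both MT phases | 62 | Yes, if attributed |
| After discharge | NICU-MT only | 62 | Yes, if attributed to the earlier MT |
| After discharge | Post-discharge MT only | 62 | Yes, if attributed |
| After discharge | No MT | 62 | No |

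During the NICU stay the whole comparator for the first randomization is silent. After discharge half of that comparator starts MT and can contribute, but only through attribution. In neither period does the committee receive counts of all serious events by arm, so rates computed from what it is sent would not be comparable.

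**What a by-arm table could show**

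The documents give no serious-event rate, so the rates below are assumptions. For two proportions at two-sided 5% with n per arm:

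power = Φ[(|p1 − p2| − 1.96 × SE0) / SE1], where SE0 = √[2 p̄(1 − p̄)/n], SE1 = √[(p1(1 − p1) + p2(1 − p2))/n] and p̄ is the mean of p1 and p2.

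With p1 = 0.20, p2 = 0.10 and p̄ = 0.15:

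- n = 125: SE0 = √(0.255/125) = 0.04517; SE1 = √(0.25/125) = 0.04472; (0.10 − 0.08853)/0.04472 = 0.257; power 60%. Expected infants with an event: 25 versus 12.5.
- n = 62 (about half of enrolment): SE0 = 0.06413; SE1 = 0.06350; (0.10 − 0.12570)/0.06350 = −0.405; power 34%.
- n = 31 (about a quarter): power 19%.

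The same formula at n = 125 over a range of assumed control risks:

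| Control risk | Power, risk doubled | Power, risk × 1.5 |
|---|---|---|
| 5% | 32% | 13% |
| 10% | 60% | 22% |
| 15% | 81% | 33% |
| 20% | 94% | 45% |

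A committee need not act on a significance test, so these powers are only a yardstick. They show that by-arm review is informative for large excesses, weak for modest ones, and weaker early in enrolment.

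**The case against.** The strongest reply is that the sentence in Section 4.4 says what must be sent and forbids nothing else. It may be meant as a rule for notifying individual cases, alongside periodic review. The committee has a broad safety remit and includes methodologists, harms are to be collected in every group, and the committee could ask for them. The document is a grant project description. Its amendment tables refer to a published protocol that is not in the file, and neither is any committee charter, so operational detail may sit elsewhere.

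Much of this stands. A reader might infer that no control event can ever reach the committee, or that it is unable to detect harm. The documents do not support that: they are silent on a by-arm flow and do not exclude one. Nor is the control rate zero by construction across the trial, because controls for one factor can receive MT through the other. Only the cell with no MT is shut out throughout. It would also go too far to say that unblinded staff make the attribution. The plan says only that treatment cannot be blinded and does not name who judges.

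The reply does not remove the gap. The sentence sets serious effects in general against those related to MT and sends only the latter to the committee. The promise to describe harms by group has no recipient and no date. A safeguard that depends on the committee thinking to ask is not one the plan provides.

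A second reply, that by-arm comparison has low power at interim looks, is correct on the figures above. It limits what the fix can achieve, but the stated route offers no such comparison at all.

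**Conclusion.** The point holds in this form: relatedness to MT is the only stated trigger for sending a serious event to the committee, and followed as written the plan gives it attribution-filtered events with no usable comparator. By this route nothing comes from about 125 of 250 participants during the NICU phase, or from about 62 throughout. The conclusion rests on the text of Sections 3 and 4.4 and on 1:1 allocation of 250 participants. It does not depend on the illustrative powers, which use assumed rates and, for the 60% figure, full enrolment. It would be answered by a charter or later protocol that gives the committee by-arm data, but none is among the documents. Because it concerns oversight of harm while infants are being treated, and an excess missed then cannot be acted on afterwards, it should be settled in the protocol.

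**What to change.** Replace the reporting sentence in Section 4.4 so that:

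- all serious adverse events and deaths in every randomized arm go to the committee at set intervals, whatever the judged relation to MT;
- they are tabulated by NICU arm and, after discharge, by post-discharge arm, with numbers at risk;
- events judged related to MT are, in addition, sent individually;
- the role that judges relatedness is named.

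The cost is a short change of text and one recurring table for the committee. It may not be free of extra data collection: the planned forms are described as covering events related to the trial, so their scope must be checked, and widened if needed, to capture serious events in every arm at all sites. As the forms are still to be developed, that can be built in from the start.
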